## **10 CLINICAL MONITORING STRUCTURE**

### **Site Monitoring Plan**

Independent trial monitors will be contracted by the UK's Medical Research Council and they will be responsible for the monitoring of this trial and compliance to ICH-GCP Guidelines. The Local Trial Monitor (LTM) of the MRC Unit in The Gambia, [name], will be a valuable resource on-site and will work collaboratively with the Sponsor's monitor.

### **Pre-study Visit**

A pre-study visit will be performed before the inclusion of the first infant in the study. This meeting will verify and document that the material to be used during the trial has been received and that the investigational team has been properly informed about the trial, regulatory requirements, and they are familiar with all the SOP requirements. The pre-study visit will be coordinated between the local and Sponsor monitors.

During this visit the Sponsor's monitor will run through the study flow with the

## **CONFIDENTIAL**

trial team alongside all the documents and ensure everyone is confident in all aspect of the trial, how it will run and how the forms need to be completed. The monitors will conduct GCP refresher training if required and also explain the safety reporting system.

### **Follow-up Visits**

The Sponsor's monitor will carry out regular follow-up visits. The Principal Investigator will be available for these visits and should allow the monitoring staff direct access to subjects' medical files and CRFs. All trial monitors are committed to professional secrecy.

During the visits, the Sponsor's monitor will:

- ☐ carry out a quality control of trial progress: respect of protocol and operating guidelines, data collection, signature of consent forms, completion of document and appearance of SAE
- ☐ sample and product management, cold chain monitoring
- ☐ review the CRFs and correspondent correction sheets
- ☐ evaluate the number of complete or ongoing study participation events

The trial monitor shall discuss any problem with the Principal Investigator and define with him / her the actions to be taken. Once the CRFs corresponding to the last visit have been completed and signed, the investigator must be available to deal with any issues raised by the trial monitor until the database is locked.

In addition to the Sponsor's trial monitor the MRC's local monitor, [name], will carry out regular meetings with the trial staff, where the documents and compliance to GCP will be checked, and feedback including advice and training recommendations will be given to the Principal Investigator.

The Sponsor's monitor will coordinate his / her visits with the local monitor and they will share their reports.

### **Close-out Visit**

A close-out visit will be performed at the end of the trial by the Sponsor's trial monitors. Its goals are to make sure that:

- ☐ The centre has all the documents necessary for archiving
- All paperwork is satisfactorily completed
- The vaccine accountability is correct and all used vials have been destroyed by MRC, Gambia

### **Audits and Inspections**

If necessary, a quality assurance audit will be carried out by independent auditors to make sure that the trial has been conducted according to the protocol and the

## **CONFIDENTIAL**

applicable regulations.

An inspection may be conducted by Regulatory Authorities.

The investigator must allow direct access to trial documents.

## **11 STATISTICAL CONSIDERATIONS**

### **11.1 Determination of the Sample Size**

No formal sample size calculation is done for the study and analyses will be mainly descriptive.

#### **Statistical Methods**

The analyses will be comparative, as clinical and laboratory data from the age-matched vaccine and untreated control groups will be compared.

### **11.2 Expected analyses and outcomes**

#### **11.2.1 Safety of MVA.HIVA**

Determined by comparing adverse events, reactogenicity, haematological and biochemical data from the MVA.HIVA recipients and controls. See Tables 2 and 3 for the probabilities of detecting events given the current trial design.

#### **11.2.2 Immunogenicity of MVA.HIVA**

Determined by comparing between Groups 1 and 2 the frequency of IFN- $\gamma$ -producing cells (by *ex vivo* and cultured ELISpot assay) in response to 15-mer peptides overlapping by 11 amino acids spanning the length of HIVA. The MVA.HIVA vaccine will be considered immunogenic in infants if at least 50% of vaccinees have detectable HIV-1-specific T cell responses at any time point after the vaccination.

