#### **Endpoints:**

For safety and reactogenicity: Actively and passively collected data on adverse events (AEs).

For immunogenicity to EPI vaccines: Antibody levels to specific vaccines.

For immunogenicity to MVA.HIVA: Frequency of IFN- $\gamma$  producing cells determined in ex-vivo (effector) and 10-day cultured (memory) ELISPOT assays after overnight stimulation with pools of HIVA-derived peptides. We shall consider the MVA.HIVA vaccine to be immunogenic in infants if at least 50% of vaccinees have detectable HIV-1-specific T cell responses at any time point after the vaccination. In the cultured IFN- $\gamma$  ELISPOT assay, a positive response is defined to be at least 250 SFU/10^6 cells above the no-peptide background, and at least 4x the no-peptide background. We shall be using standardized and trial-tested assays, which have been described in Goonetilleke et al. [48]. MVA.HIVA alone is not considered to be a strong priming vaccine, but it can strongly and consistently boost HIV-1-specific T cell responses if they have been previously primed [20, 21, 47, 48]. It is planned in the future to use the MVA.HIVA vaccine as a booster to a BCG.HIVA prime, which should enhance the generation of HIV-specific T cell levels after the MVA.HIVA vaccination.

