**CONFIDENTIAL****4.1 Sample size:**

A total of 48 mother-infant couples will be enrolled into the study and randomized in two groups of 24.

**Group 1:** MVA.HIVA administered at 20 weeks of age (n=24)

**Group 2:** Normal EPI vaccine schedule (control group) (n=24)

This study is a pilot study and the immunogenicity analyses will be mainly descriptive. As such, it is not powered to provide definitive evidence of vaccine-induced effects; rather it is based on smaller numbers of participants and will only indicate trends, feasibility, or size of effect and variability of measurements to inform the design of more definitive studies. The rate of serious adverse events will be used as one measure of the safety of the candidate vaccine. Table 2 shows examples of sample size calculations for safety in terms of the ability to detect SAEs, i.e. the probabilities of observing 0, 1+ (1 or more), 2+ or 3+ SAEs among group of n=24 for a range of possible true event rates. If none of the 24 volunteers receiving the vaccine experiences an SAE definitely related to the vaccine, the 95% two-sided upper confidence bound for the rate of such reactions in the population is 13.8% (Table 3).

**Table 2.** Probabilities of detecting events for n=24

| Event rate (SAE) | Detect. Probability (0 events/24 vol's) | Detect. Probability (1+ events/24 vol's) | Detect. Probability (2+ events/24 vol's) | Detect. Probability (3+ events/24 vol's) |
|------------------|-----------------------------------------|------------------------------------------|------------------------------------------|------------------------------------------|
| 0.010            | 0.88                                    | 0.11                                     | 0.01                                     | <0.01                                    |
| 0.025            | 0.74                                    | 0.26                                     | 0.03                                     | <0.01                                    |
| 0.035            | 0.65                                    | 0.35                                     | 0.06                                     | 0.01                                     |
| 0.050            | 0.54                                    | 0.46                                     | 0.12                                     | 0.02                                     |

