### **Visit 2 – BASELINE VISIT (Infant aged 19 weeks $\pm$ 10 days)**

- Subjects will be brought to the vaccine trial clinic.
- Continued consent to participate in the study will be confirmed.
- Inclusion and exclusion criteria will be checked.
- An interim medical history will be taken.
- Physical examination including vital signs (temperature, respiratory rate, pulse rate), and anthropometry (weight, mid left upper arm circumference (MUAC), length) will be performed by the research field worker / research nurse.
- 5 mL of venous blood will be collected for baseline FBC, biochemistry, pre-MVA.HIVA immunogenicity and EPI vaccine antibody assays.
- Appointment given for 1 week time.

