**CONFIDENTIAL**

- 5 mL of venous blood will be collected for FBC, biochemistry, MVA.HIVA immunogenicity and EPI vaccine antibody assays.
- Appointment at the clinic will be given for 7 weeks time.

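### The 50% responder rule for calling MVA.HIVA immunogenic has no week-19 or control-group condition, so meeting it does not show that the vaccine caused the responses

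*Protocol*

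**What the plan says.** Section 3 (Endpoints) sets the criterion: "We shall consider the MVA.HIVA vaccine to be immunogenic in infants if at least 50% of vaccinees have detectable HIV-1-specific T cell responses", with any post-vaccination visit qualifying. Section 11.2.2 repeats it, calling the vaccine "considered immunogenic in infants if at least 50% of vaccinees have detectable HIV-1-specific T cell responses at any time point after the vaccination". The sentence before it in 11.2.2 says immunogenicity is determined by comparing IFN-γ-producing cell frequencies between Groups 1 and 2. Section 11.1 (Statistical Methods) also calls the analyses comparative. Nothing says how the comparison and the 50% rule combine.

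Two assays supply the data: "ex-vivo (effector) and 10-day cultured (memory) ELISPOT assays after overnight stimulation with pools of HIVA-derived peptides". Positivity is defined for one of them: "In the cultured IFN- $\gamma$ ELISPOT assay, a positive response is defined to be at least 250" SFU per million "cells above the no-peptide background, and at least 4x the no-peptide background". The ex vivo assay has no cut-off, and the rule does not say which assay counts.

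Baseline and control data are planned. Visit 2 (week 19) provides: "5 mL of venous blood will be collected for baseline FBC, biochemistry, pre-MVA.HIVA immunogenicity and EPI vaccine antibody assays". Table 7 schedules MVA.HIVA immunogenicity at weeks 19, 21, 28 and 36. Table 6 has both groups bled at all four. Section 4.2 (Masking) keeps assay staff unaware of allocation. On size: "A total of 48 mother-infant couples will be enrolled into the study and randomized in two groups of 24".

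**The concern.** Safety and immunogenicity together form the primary objective, and the 50% rule is the protocol's only stated pass mark for immunogenicity. A pass mark should fail when the vaccine has done nothing. This one need not, because it looks neither at what the infants showed before vaccination nor at what unvaccinated infants of the same age show in the same masked assays.

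Allowing a response at any of three visits gives each infant several chances to be scored positive for reasons other than the vaccine. Section 2.2.6 reports that MVA.HIVA alone gave no detectable ex vivo response and cultured responses in 5 of 8 healthy volunteers. A true rate near the 50% bar is therefore plausible, and that is where a few non-specific positives could decide the outcome. The word "immunogenic" could then be carried into later studies without support from the randomised comparison.

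**Working it through.** **1. The rule on its own terms (no assumption needed).** Half of 24 is 12. If 12/24 vaccinees and 12/24 controls are positive, the rule is met, although the two-sided Fisher p-value for the difference is 1.0. If 12 vaccinees are positive after vaccination and all 12 were positive at week 19, it is also met.

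**2. Chance of meeting the rule with no vaccine effect.** The protocol states no error rate for the rule, so there is no figure to reproduce.
- From the protocol: n = 24 vaccinees; three post-vaccination visits (weeks 21, 28, 36); threshold 12.
- Assumed: a false-positive rate f per test, with independent tests.
- Chance that one infant is ever positive over k tests: q = 1 − (1 − f)^k.
- Chance the rule is met: P = Σ C(24,x) q^x (1 − q)^(24−x), for x = 12 to 24.

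Example with k = 3 and f = 0.10: q = 1 − 0.9³ = 0.271 and P = 0.014.

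| f per test | q, one assay (k = 3) | P | q, either assay (k = 6) | P |
|---|---|---|---|---|
| 5% | 14.3% | 0.004% | 26.5% | 1.2% |
| 10% | 27.1% | 1.4% | 46.9% | 46% |
| 15% | 38.6% | 17% | 62.3% | 92.5% |
| 20% | 48.8% | 53% | – | – |

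Half of unvaccinated infants would count as responders at f = 20.6% with k = 3 (1 − 0.5^(1/3)), or 10.9% with k = 6 (1 − 0.5^(1/6)).

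**3. A narrower reading.** If the rule means 50% positive at one and the same visit, then at f = 20% each visit passes with probability 0.00098. Over three visits the chance is 1 − (1 − 0.00098)³ = 0.3%. It is 9.1% at f = 30% and 51% at 40%. The text does not exclude this reading.

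**4. Weak true priming.** With a true response of 30% and k = 3, q = 1 − 0.7(1 − f)³. This gives q = 0.300, 0.490 and 0.570 at f = 0, 10% and 15%. The rule is met with probability 0.03, 0.54 and 0.82.

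**5. A rule with baseline and control conditions.** A responder must be negative at week 19, and an infant positive then stays in the denominator as a non-responder. With true response t and k = 3:
- Group 1: r1 = (1 − f)[1 − (1 − t)(1 − f)³]
- Group 2: r2 = (1 − f)[1 − (1 − f)³]

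At t = 0.625 (the 5/8) and f = 0.10: r1 = 0.9 × 0.727 = 0.654 and r2 = 0.9 × 0.271 = 0.244. P(claim) sums the product of the two binomial probabilities over all (a, b), where a and b are the responder counts in Groups 1 and 2, with a ≥ 12 and either a > b alone or a > b with two-sided Fisher p < 0.05.

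| True response | f | Current rule | ≥ 50% and a > b | ≥ 50% and Fisher p < 0.05 |
|---|---|---|---|---|
| none | 10% | 1.4% | 0.6% | 0.2% |
| none | 15% | 17% | 5.8% | 0.8% |
| none | 20% | 53% | 16% | 1.2% |
| 62.5% | 0 | 0.93 | 0.93 | 0.93 |
| 62.5% | 5% | 0.98 | 0.95 | 0.92 |
| 62.5% | 10% | 0.995 | 0.96 | 0.77 |
| 62.5% | 15% | 0.999 | 0.95 | 0.55 |

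**The case against.** Several stronger readings are tempting, and the protocol does not support them.

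- **That the controls are ignored.** They are not: section 11.2.2 plans a Group 1 versus Group 2 comparison of frequencies, and 12/24 against 12/24 would be visible there. The two sentences can be read as a comparison plus a minimum responder level. What stands is that the protocol does not say so, and the 50% sentence is worded as sufficient by itself.
- **That assay background alone can meet the rule.** For the cultured assay, the margin of 250 SFU and the fourfold requirement already deal with no-peptide background. Only peptide-driven or otherwise non-specific positives remain, plus an ex vivo assay without a cut-off. The infants have HIV-uninfected mothers, and nothing in the protocol suggests a high rate of such positives.
- **That a false claim is likely.** At 5% per visit on one assay the risk is negligible. Positive correlation between an infant's visits would lower the any-of-three rate for the same f.
- **That this is a go/no-go gate.** The protocol ties no development decision to the rule. Section 4.1 calls the trial a pilot, with immunogenicity analyses mainly descriptive and no power for definitive evidence. A compulsory significance test would therefore be debatable.

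A separate analysis plan, not available here, could define responder derivation and baseline handling. It would still inherit a pass mark that the protocol states twice without either condition. The descriptive label does not help, because the protocol chose a categorical verdict.

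**Conclusion.** The concern holds in a limited form. As written, the rule can call MVA.HIVA immunogenic when controls respond equally often, or when the infants counted were already positive before vaccination. That follows from the text alone.

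How often it would happen cannot be known from the protocol. With independent tests, the risk becomes appreciable at about 15–20% false positives per visit if one assay counts, or about 10% per test if either assay counts; below that it is small. The narrower same-visit reading would need higher rates still. The practical weakness is that a pass could not be attributed to the vaccine from the rule itself, although the data needed to attribute it are already being collected.

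**What to change.** In sections 3 and 11.2.2:

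1. Define a responder as an infant positive at week 21, 28 or 36 and not positive at week 19. State that visits are pooled within infant.
2. Name the assay that counts. If the ex vivo assay counts, give its cut-off.
3. Score Group 2 by the same rule at the same visits.
4. Call the vaccine immunogenic only if at least 50% of Group 1 respond and the Group 1 proportion exceeds that of Group 2. Report both proportions and their difference with 95% confidence intervals.

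Whether the interval must also exclude zero is the sponsor's choice in this pilot. A numerical excess costs little but protects less at high background. A formal criterion protects well but loses real positives: at 62.5% true response and 15% background, the chance of the claim falls from 0.999 to 0.55. With Fisher's test, 12/24 against 4/24 passes (p = 0.030) and 12/24 against 5/24 does not (p = 0.069). With little or no background, neither version costs much.

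No new samples, visits or assays are needed for the control and baseline conditions. The wording should be settled before allocation is linked to the assay results.

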#### **11.2.3 Immunogenicity of EPI vaccines**

The MVA.HIVA will be given at week 20 (4 weeks after the last EPI vaccines) so as to avoid the possibility of vaccine interference. However, vaccine antibody levels will be measured one week before and one week after MVA.HIVA (i.e. 5 weeks after the last EPI vaccines) to assess for gross interference of the MVA.HIVA vaccine with the immunogenicity of the EPI vaccines. Antibody responses to the EPI vaccines will be compared between Groups 1 and 2, with particular focus on the immunogenicity of Hib, which is the least immunogenic of the EPI vaccines and for which antibody levels below 0.5 micrograms per litre are considered unprotective.

### **11.3 Data Management**

[name] will be the data manager with overall responsibility for receiving, entering, cleaning, querying, analysing and storing all data that accrues from the study. The data will be entered into the subjects' CRFs and will be transferred by double entry with verification to a secure database.

**CONFIDENTIAL**

## **12 SOURCE DOCUMENTS AND ACCESS TO SOURCE DATA/DOCUMENTS**

The investigators will maintain appropriate medical and research records for this trial, in compliance with ICH GCP Guidelines and regulatory and institutional requirements for the protection of confidentiality of subjects. The Principal Investigator, co-investigators and clinical research nurses will have access to records.

The investigators will permit authorized representatives of the Sponsor, Ethics Committees, independent auditors and regulatory agencies to examine clinical records for the purposes of quality assurance reviews, audits and evaluation of the study safety and progress.

All protocol required information will be collected in Case Report Forms (CRF) designed by the Principal Investigator in collaboration with the data manager. All source documents e.g. blood result forms, radiology reports, copies of EPI vaccination cards will be filed separately and be available for review if needed.

All data on the CRFs must be legibly recorded in blue or black ink or typed. A correction should be made by striking through the incorrect entry with a single line and entering the correct information adjacent to it. The correction must be initialed and dated by the investigator or a designated, qualified individual.

Any requested information that is not obtained as specified in the protocol should have an explanation noted on the CRF as to why the required information was not obtained.

## **13 QUALITY CONTROL AND QUALITY ASSURANCE**

Data will be evaluated for compliance with protocol and accuracy in relation to source documents. The study will be conducted in accordance with procedures identified in the protocol. SOPs will be used at all clinical and laboratory sites. Regular monitoring will take place according to ICH-GCP Guidelines, and an independent audit may be performed. Following written standard operating procedures, the monitors will verify that the clinical trial is conducted and data are generated, documented (recorded), and reported in compliance with the protocol, GCP, and the applicable regulatory requirements. The clinical trial site will provide direct access to all trial related facilities, source data/documents, and reports for the purpose of monitoring and auditing by the Sponsor, and inspection by local and regulatory authorities.

## **14 ETHICS/PROTECTION OF HUMAN SUBJECTS**

This protocol will be approved by the Gambia Government / MRC Joint Ethics Committee, Oxford Tropical Research Ethics Committee, the Sponsor (MRC-UK), Stockholm Regional Ethics Committee, International Aids Vaccine initiative and the funder (EDCTP) before this study commences. This trial will be conducted in accordance with the current revision of the Declaration of Helsinki, and with the International Conference on Harmonisation Good Clinical Practice (ICH-GCP)

## **CONFIDENTIAL**

guidelines (E6) and regulations.

### **14.1 Informed Consent Process**

Written informed consent will be obtained from a parent of all infants in the study. Fathers will be actively involved in the consent process. The consent form to be used will have been approved by the relevant ethics committees. The information sheet and consent form will be translated into Mandinka and Wolof to aid the consent process, and the translated versions will be back translated by an independent translator to ensure accuracy of the translation. Translated information sheets will be made available to the study participants as required. For those parents without fluent English language skills, a field worker who speaks their language will be assigned for all visits and an assigned impartial witness will observe the consent process in accordance with ethical requirements. The subjects may withdraw consent at any time throughout the course of the trial. A copy of the informed consent document will be given to the parents for their records. The rights and welfare of the infants will be protected by emphasizing to the parents that the quality of their medical care will not be adversely affected if they decline to participate in this study.

### **14.2 Subject Confidentiality**

All records will be kept in locked filing cabinets, and accessed only by the investigators and the study nurses / field workers. The CRFs will record the infant's 3-digit identification number and initials, and the subject's name will not appear on the form. All computer entry and networking programs will be done with coded numbers and initials only. Only the investigator's team, the trial monitors and representatives of the Sponsor, Ethics Committees, independent auditors and regulatory authorities will have access to the records. Photographs taken of vaccination sites (with the subject's written informed consent) will not include the infant's face and will be identified by the infant's 3-digit identification number only. Digital photographs will be stored as confidential records as above. This material may be shown to other professional staff or be used for educational purposes, or be included in a scientific publication. Every effort will be taken to maintain confidentiality.

